## Abstract

**Clinical trial registration:**

clinicaltrials.gov, identifier: NCT06314464.

## Introduction

Mild traumatic brain injury (mTBI) is a prevalent issue among military service members (SMs) (1), often resulting in persistent vestibular dysfunction that is increasingly linked to cognitive and proprioceptive impairments, which can further compromise a SM's operational capabilities (2–4). Advancing recovery strategies for SMs post-mTBI is paramount to ensuring military readiness and safety. Sensory, motor, and cognitive deficits following mTBI can significantly impair a SM's ability to perform critical warrior tasks, such as moving under fire and maintaining situational awareness, which are essential for combat effectiveness and survival (3, 5). Despite the availability of various rehabilitation techniques, there remains a critical need for interventions that not only address these multifaceted impairments but also translate into tangible improvements in operational performance. Current return-to-duty (RTD) decisions often rely on self-reported symptoms and standardized physical and cognitive tests that may not accurately reflect the functional demands of military activities (6–9). This highlights a significant gap in rehabilitation approaches: the lack of objective, ecologically valid tools that address both the physical and cognitive demands of military tasks while being accessible and portable for widespread use.

Current rehabilitation techniques, such as the Computer-Assisted Rehabilitation Environment (CAREN; Motek Medical, Houten, Netherlands) and tablet-based tools like VestAid (BlueHalo, Germantown, MD), have shown promise in addressing vestibular dysfunction. The CAREN is a large, virtual reality (VR) system that combines multi-planar motion with immersive virtual environments projected onto a curved, panoramic screen. It utilizes a motion capture system to track movement in real time and can be customized to stimulate the vestibular, somatosensory, and visual systems. Within the Military Health System, the CAREN has been successfully utilized to treat vestibular and balance deficits in SMs with mTBI (10). Moreover, performance on immersive balance tasks in the CAREN has been shown to distinguish SMs with comorbid mTBI and post-traumatic stress disorder (PTSD) from those with mTBI alone, suggesting that leveraging virtual environments in the CAREN may provide greater insight into vestibular complaints and more targeted interventions (11). However, the CAREN's large physical footprint, high cost, and need for a specialized engineer operator to build the scenarios and run the system limit its accessibility and scalability. VestAid is a tablet-based technology developed for vestibular rehabilitation, using the device's camera to track head and eye movements and provide real-time feedback for patients and clinicians (12). While VestAid is portable, it lacks the immersive, multisensory integration necessary for comprehensive rehabilitation. These limitations underscore the need for a novel rehabilitation system that is low-cost, portable, and capable of delivering immersive, ecologically valid rehabilitation tailored to military-specific tasks.

To address this gap, we developed Praxis (BlueHalo, Germantown, MD), a novel, portable system incorporating low-cost wearable sensors and a VR environment, designed to deliver effective multisensory rehabilitation exercises that hold military face validity. This innovative approach aims to bridge the gap between traditional rehabilitation techniques and real-world demands faced by SMs. Three VR scenarios were designed to enhance gaze stability, balance, and cognitive-motor integration. Unlike other VR-based systems, Praxis is uniquely designed to deliver dual-task and multisensory exercises that mirror the operational challenges faced by service members while remaining accessible and scalable for widespread use.

Research indicates that vestibular dysfunction post-mTBI corresponds with increased centrality in key brain regions including the frontal cortex, cingulate eye field nodes, and visual cortex (2, 4). These findings indicate that rehabilitation must encompass more than just physical recovery; it should also address cognitive, visual, and proprioceptive domains to facilitate comprehensive recovery. Targeted interventions that encourage SMs to shift from visual to proprioceptive feedback during tasks may accelerate recovery, as suggested by Smith et al. (4). Furthermore, evidence from Dieterich et al. demonstrate the brain's ability to reallocate resources in response to vestibular deficits, reinforcing the potential for targeted rehabilitation to effectively reprogram brain function (13). Resting-state functional magnetic resonance imaging (rs-fMRI) studies further emphasize the relationship between vestibular rehabilitation and neurophysiological improvements as seen in patients with vestibular migraine (14). Changes in spontaneous brain activity, measured by fractional amplitude of low-frequency fluctuation (fALFF), correlated with patient-reported improvements in dizziness and other impairments, suggesting that similar neurophysiological markers could be monitored in SMs undergoing multisensory rehabilitation for mTBI. Quantifying these changes and correlating them with functional improvements in real-world tasks, such as those encountered in military training and operations, could provide critical insights into the effectiveness of multisensory rehabilitation strategies (15, 16). Additionally, functional connectivity changes observed during recovery from mTBI further support the notion that targeted rehabilitation can induce measurable brain plasticity that corresponds with recovery (17, 18). By incorporating advanced neuroimaging techniques, such as rs-fMRI, this study aims to quantify neurophysiological changes associated with Praxis rehabilitation, providing possible evidence of neuroplasticity alongside objective measures of Praxis effectiveness in improving functional performance.

The primary goals of this pilot study are twofold: 1) to evaluate the feasibility of using the Praxis system to deliver VR, military-specific multisensory rehabilitation to a representative sample of SMs with vestibular-related complaints post-mTBI over a four-week period, and 2) to evaluate objective measures, including advanced neuroimaging, to support RTD decisions by correlating functional performance improvements with neurophysiological changes. This dual focus ensures that Praxis not only addresses the immediate rehabilitation needs of SMs but also provides measurable, objective data to guide RTD decisions. The inclusion of objective, robust, and sensitive assessments enabled by recent advances in wearable sensor technology (19–24) will be critical in determining the added value of the Praxis system in a military medicine context.

Our secondary aim is to explore the relationship between Praxis scores, self-reported questionnaires, functional performance on military-specific tasks, self-reported symptom severity, neurophysiological changes, and rehabilitation compliance. By analyzing these metrics, we aim to provide preliminary insights into the effectiveness of Praxis in detecting and influencing measurable changes in readiness performance during recovery from mTBI. The insights gained from this study could pave the way for larger trials, aimed at changing the approach of post-mTBI rehabilitation and ensuring that SMs are fully prepared for the demands of their warfighter duties upon return to active service. The findings from this study will lay the groundwork for larger trials, potentially enhancing post-mTBI rehabilitation and military readiness assessments.

## Methods

This is a prospective study of a Control and a Praxis group to determine if a novel multi-sensorimotor and vestibular training program results in enhanced functional outcomes in the military population. This study has been registered on ClinicalTrials.gov (NCT06314464). It was approved by the San Antonio Institutional Review Board (C.2023.055) and the U.S. Army Medical Research and Development Command, Office of Human Research Oversight. The patients/participants will provide their written informed consent to participate in this study.

## Participants

Fifteen SMs with a self-reported history of mTBI and unresolved vestibular-related complaints from the Center for the Intrepid's Special Operations Performance and Recovery (SPaR) Program at Brooke Army Medical Center will take part in a multisensory vestibular rehabilitation program. These participants will undergo a 4-week exercise program that includes gaze stabilization, dual-task balance exercises, spatial navigation, and agility training delivered via Praxis VR software in addition to the standard SPaR Program treatments. Another group of 15 SMs, who will not participate in the multisensory rehabilitation but will instead receive the standard SPaR Program treatments, will serve as the Control group. The Control group will consist of SMs who may or may not have a history of mTBI but do not report persistent vestibular-related complaints (i.e., dizziness or imbalance), allowing for comparison to individuals without vestibular dysfunction and providing normative data for self-reported symptom severity and functional performance on military-specific tasks in this unique population. All SPaR participants, including those in the Praxis group and the Control group, complete a comprehensive performance program that includes musculoskeletal injury rehabilitation, nutritional assessment, and psychological assessment and treatment. Recruitment efforts will focus on ensuring diversity in sex, ethnicity, and socioeconomic status to ensure that the sample is representative of and applicable to the broader military population.

### Inclusion criteria

Participants in the Praxis group will be those involved in the SPaR Program, aged 18–50 years, with either a self-reported or clinician-confirmed diagnosis of mTBI [as defined in the VA/DoD Clinical Practice Guideline for Management and Rehabilitation of Post-Acute mTBI (25)], and who continue to experience dizziness or imbalance. Additionally, they must be right-handed, as assessed by the Edinburgh Handedness Inventory-Short Form (26). As a pilot study with limited sample size, we chose to exclude left-handed subjects to reduce data variations. Given significant differences in functional brain localization between left- and right-handed individuals (27), particularly in motor (28) and language areas (29), such a focused inclusion can provide a more homogeneous sample, potentially increasing our statistical power. Additionally, this selection aligns with the technical constraints of our current VR system, which displays a right-handed firearm, and the hardware configuration, which includes a replica M4 rifle that houses only the right-hand VR controller. Presenting left-handed users with a right-handed physical and virtual weapon could create visuomotor discordance and disorientation, potentially compromising both the user experience and data quality. The Control group participants will also be from the SPaR Program, within the same age range, with or without a history of mTBI but without current complaints of dizziness or imbalance.

### Exclusion criteria

Participants will be excluded if they have any cognitive impairment (e.g., altered mental capacity due to administration of any mind-altering substances or significant stress/life circumstances, as assessed by standardized neuropsychological tests or clinician judgment), exhibit behavior that could compromise data collection or safety during the study, report severe pain during the evaluation (7/10 on a subjective pain scale), are pregnant (due to balance-related concerns; a pregnancy test will be administered for women of childbearing potential who are not using an acceptable form of contraception), or cannot refrain from alcohol or medications that might affect their balance or cerebral blood flow within 24 h prior to rs-fMRI and other repeat testing. Additionally, those who are mixed or left-handed as determined by the Edinburgh Handedness Inventory-Short Form (26), or those who cannot undergo MRI (e.g., due to non-MRI compatible devices, embedded metal fragments, or severe claustrophobia) for the Praxis group undergoing rs-fMRI will also be excluded. PTSD is not an exclusion criterion unless it results in cognitive impairment or unsafe behavior, ensuring that the sample remains representative of the broader military population with mTBI.

To ensure the Control group provides an adequate comparison, both groups will undergo the same baseline and follow-up assessments, including functional performance tests and self-reported symptom measures. This design allows for direct comparison of outcomes between SMs with and without persistent vestibular dysfunction, providing insights into the specific effects of vestibular rehabilitation. Furthermore, any group differences identified will inform future studies by highlighting the unique contributions of vestibular rehabilitation to functional recovery post-mTBI, potentially guiding clinical approaches for SMs with and without vestibular complaints.

## Study procedures

### Outlined study procedures

Following enrollment, each participant will be provided with an Oura ring™ (Oura Health Oy; San Francisco, CA) to wear throughout the study period. All participants will then complete the baseline Readiness Assessment Battery. Those in the Praxis group will also undergo a baseline rs-fMRI scan. Over the next 4 weeks, the Praxis group will participate in the SPaR Program combined with 45 min of supervised Praxis therapy daily, 5 days a week, in addition to a home exercise program (HEP) consisting of 20 min of unsupervised VestAid therapy daily, 5 days a week. VestAid is a tablet-based technology designed to support vestibular rehabilitation by monitoring and guiding patients through vestibulo-ocular reflex (VORx1) exercises (12). Participants in the Praxis group report progress at the end of each week (four times) using a Global Rating of Change (GROC) (30). The Control group participants will complete 4 weeks of the SPaR Program without a HEP. At the 4-week follow-up, all participants will retake the questionnaires and the Readiness Assessment Battery. Those in the Praxis group will undergo a follow-up rs-fMRI scan and will be asked to evaluate their experience with the Praxis system using the SUS. Over the course of the study, Praxis group participants will engage in approximately 20 sessions of Praxis and VestAid (5 days a week for 4 weeks).

### Detailed study procedures

#### Baseline assessment

Demographic information [including age, sex, height, weight, body mass index (BMI), Military Occupational Specialty/Area of Concentration (MOS/AOC), time in service, number and duration of deployments, number of self-reported and clinician-confirmed mTBI incidents and their causes, support structure (e.g., single, married), history of migraines/headaches, history of attention deficit hyperactivity disorder and/or learning disorders, and medical/surgical history] will be collected from all participants.

##### Questionnaires

The following self-reported questionnaires will be administered: the Dizziness Handicap Inventory (DHI) (31, 32), Pittsburgh Sleep Quality Index (PSQI) (33), Generalized Anxiety Disorder scale (GAD-7) (34), Post-Traumatic Stress Disorder Check List—Military Version (PCL-M) (35), Vestibular Activities Avoidance Instrument-9 (VAAI-9) (36), Headache Impact Test-6 (HIT-6) (37), perception of fogginess [assessed on a scale of 0 to 10 as per the Vestibular/Ocular Motor Screening (VOMS) (38)] to measure this symptom as a known indicator of multiple-domain adverse effects in athletes post-mTBI (39), and the Santa Barbara Sense of Direction Scale (SBSOD) (40). Participants will also rate their current functional level on a scale from 0 to 100, with 100 indicating optimal function (41).

##### Readiness Assessment Battery

All participants will undergo an assessment battery that includes the 4-Item Hybrid Assessment of Mobility for mild Traumatic Brain Injury (HAM-4-mTBI) (42), modified version of the Portable Warrior Test of Tactical Agility (POWAR-TOTAL) (43, 44), 5-10-5 Shuttle Run (45), and 300-yard Shuttle Run (45, 46) tests. Opal inertial sensors and Mobility Lab software (APDM™ wearable technologies, Portland, OR) will be used for all assessments to record objective outcomes. The Opal inertial sensors are worn on the forehead, sternum, lumbar spine, non-dominant wrist, and dorsum of each foot during the assessment battery. Opal-based outcome measures will include: peak lumbar turning speed (peak angular rate of the pelvis in the transverse plane); head turning speed (peak angular rate of the head in the transverse plane); upper trunk turning speed (peak angular rate of the upper trunk in the transverse plane); head-body coordination timing (peak angular displacement between the head and the trunk measured just before or at the onset of trunk axial rotation during turning, measured in the transverse plane); and head turn symmetry (left-to-right head turn velocity ratio).

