###### HAM-4-mTBI

The HAM-4-mTBI (42) is a condensed, hybrid mobility assessment based on the Functional Gait Assessment (FGA) (47) and the High-Level Mobility Assessment Tool (HiMAT) (48) to monitor individuals with mTBI. Participants will complete the FGA gait with horizontal head turns and gait with pivot turn, as well as the HiMAT fast forward and backward walk. Outcomes measured from the HAM-4-mTBI will include the Opal-based measures plus the FGA gait with horizontal head turns and gait with pivot turn scored according to FGA criteria (scored 0 to 3) and the HiMAT fast forward and backward walk scored according to HiMAT criteria (middle 10 m of a 20 m trial is timed, scored 1 to 4).

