#### Relationships between neuroimaging changes and behavioral outcomes

Correlation analyses will be performed to examine the relationships between rs-fMRI findings and behavioral outcomes (from questionnaires and the Readiness Assessment Battery tasks: HAM-4-mTBI, modified version of the POWAR-TOTAL, 5-10-5 Shuttle Run, and 300-yard Shuttle Run), as well as clinical characteristics, with a significance threshold set at *p* < 0.05.

By comparing the behavioral outcomes from questionnaires and the Readiness Assessment Battery between baseline and post-rehabilitation, this study aims to identify any significant changes occurring between these assessment points. To compare between-group differences in behavioral outcomes, improvements during the 4-week intervention will be calculated by subtracting the baseline value (the first visit) from the post-rehabilitation value. A general linear model will be used to assess between-group differences in primary and secondary outcomes. Estimated marginal means, standard errors (SEs), 95% confidence intervals, and effect sizes will be reported for the outcomes derived from the general linear model. Effect sizes will be interpreted as small (0.01), medium (0.06), and large (0.14) (62). The Minimum Clinically Important Difference (MCID) will be calculated for all outcomes using the equation MCID = SD ^*^ 0.2.

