We additionally propose that the Praxis group's behavioral outcomes following the 4-week intervention will meet or exceed those of the Control group, which serves as a normative reference for self-reported symptom severity and functional performance on military-specific tasks in this unique population. To examine this, we will compare between-group differences at the 4-week timepoint. The Control group will establish the presumed reasonable thresholds for RTD decisions. We will report the number of individuals in the Praxis group who meet or exceed these thresholds. The team plans to investigate the relationship between participants' Praxis scores, behavioral outcomes, and the underlying neurophysiological changes throughout recovery from mTBI, using neuroimaging biomarkers identified in prior studies (4, 14, 18). Specifically, we will test the hypothesis that improvements in behavioral outcomes are associated with enhanced abilities as measured by Praxis scores, as well as functional changes observed through rs-fMRI. We extend this hypothesis by suggesting that if performance on Praxis exercises predicts improvements in behavioral outcomes, it does so in a manner that could be linked to detectable changes in the underlying neurophysiology. To test this, the team will conduct a mediation analysis, which is a regression-based method to assess how error propagates through multiple related variables by evaluating the likelihood of alternative models that include primary and mediating variables.

A potential challenge of our study design is the need for significant correlations between the measures being tested to justify a mediation analysis. Given that our study is the first of its kind, it is not guaranteed that the performance on Praxis exercises and the neurophysiological measures will correlate with improvements in behavioral outcomes. To mitigate this risk, the team plans to conduct a series of secondary analyses to derive as many insights as possible from this pilot study. First, the team will evaluate the functional neuroimaging data to test hypotheses established in previous studies. Second, the team will explore whether there are neurophysiological features related to Praxis performance that do not manifest in the behavioral outcomes.

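### Head turn symmetry is a left-to-right ratio that is best near 1, but it is scored as post minus baseline, so left- and right-sided recoveries offset each other

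*Protocol article*

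**What the plan says.** The Readiness Assessment Battery section of the protocol article defines five measures from the Opal sensors. The last is "head turn symmetry (left-to-right head turn velocity ratio"). The order of the sides is fixed as left over right; it is not weaker over stronger.

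Each battery test takes these measures as outcomes. For the mobility test the wording is "Outcomes measured from the HAM-4-mTBI will include the Opal-based measures plus the FGA gait with horizontal head turns", and the sections on the POWAR-TOTAL and the two shuttle runs do the same.

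Under Relationships between neuroimaging changes and behavioral outcomes, battery results count as behavioral outcomes ("By comparing the behavioral outcomes from questionnaires and the Readiness Assessment Battery between baseline and post-rehabilitation"). For the group comparison, "improvements during the 4-week intervention will be calculated by subtracting the baseline value (the first visit) from the post-rehabilitation value", and "A general linear model will be used to assess between-group differences in primary and secondary outcomes". The same section correlates rs-fMRI findings with battery outcomes.

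Under Praxis performance as a marker of recovery, the Control group supplies reference thresholds, and "We will report the number of individuals in the Praxis group who meet or exceed these thresholds".

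On side of deficit, the inclusion criteria ask only for people "who continue to experience dizziness or imbalance". Nowhere does the article fold the ratio, measure its distance from 1, or exempt it from the subtraction.

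**The concern.** Post minus baseline measures improvement only on a scale with one good direction. It does not matter whether that direction is up or down: for a run time, a negative change is simply the good one. A left/right ratio has no such direction. Someone slow to the left starts below 1 and improves by rising; someone slow to the right starts above 1 and improves by falling. Averaging the two estimates a net shift of side, not a gain in symmetry.

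The same feature affects any correlation that uses change in the ratio, because a larger change is not a better one. It also affects the threshold count. Against a Control reference near 1, a participant at 1.25 passes and the mirror-image participant at 0.80 fails, although they are equally asymmetric.

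What is at stake is one objective measure of head turning, repeated across four tests. It could show little or no change in a group that had in fact become more symmetric.

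**Working it through.** **Plan's own figure.** There is none to reproduce. The 15 per group rests on feasibility, and no power is stated for this outcome.

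**Inputs from the article.** Ratio = left velocity / right velocity; change = post minus baseline; 15 in each group; significance level 0.05, taken as two-sided; side of deficit unrestricted.

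**Inputs assumed.** Size of asymmetry, mix of sides, measurement error and degree of recovery are not in the article, so a range is shown.

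**Step 1: two mirror-image participants.** The mirror image of 0.80 is 1/0.80 = 1.25.
- 0.80 to 1.00: change = 1.00 - 0.80 = +0.20
- 1.25 to 1.00: change = 1.00 - 1.25 = -0.25
- On the folded scale both start at |ln 0.80| = ln 1.25 = 0.223 and end at 0, so both change by -0.223.

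**Step 2: group mean, all 15 recovering fully, no measurement error.** Mean raw change = (n_left × 0.20 - n_right × 0.25)/15.

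| Left / right deficits | Mean raw change | Mean change in \|ln ratio\| |
|---|---|---|
| 15 / 0 | +0.200 | -0.223 |
| 12 / 3 | +0.110 | -0.223 |
| 10 / 5 | +0.050 | -0.223 |
| 8 / 7 | (1.60 - 1.75)/15 = -0.010 | -0.223 |
| 7 / 8 | (1.40 - 2.00)/15 = -0.040 | -0.223 |

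Cancellation is not exact on the raw scale, because 0.80 and 1.25 are not equally far from 1; an exactly even mix leaves (0.20 - 0.25)/2 = -0.025. A log without the absolute value does not cure this: at 8/7 the mean log change is only +0.015.

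**Step 3: dependence on the mix of sides.** Simulated comparison of change scores, 15 against 15, full recovery from 0.80 or its mirror, error SD 0.08 on the log scale per visit, Controls symmetric and unchanged. Power on the raw ratio is 6% at 50% left-sided, 11% at 65%, 42% at 80% and 99.8% at 100%. On |ln ratio| it is 99.9% throughout.

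**Step 4: partial recovery from varied asymmetry.** Same comparison, but with true baseline ln ratio normal around 0 (an even mix), asymmetry cut by 60%, error SD 0.08, and Controls near-symmetric (true ln-ratio SD taken as 0.05).

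| Assumed ln-ratio SD in the Praxis group | Power, raw ratio | Power, \|ln ratio\| |
|---|---|---|
| 0.25 | 6% | 73% |
| 0.15 | 5% | 34% |
| 0.10 | 5% | 15% |

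The raw ratio stays at about the false-positive rate. The gain from folding shrinks as asymmetry gets smaller.

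**Step 5: what folding costs.** A perfectly symmetric person measured with log error SD 0.08 has an expected |ln ratio| of 0.08 × √(2/π) = 0.064, not 0. With asymmetry of 0.90, error SD 0.08 and every deficit on one side, simulated power is 67% on the raw ratio against 38% on the folded one.

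**The case against.** The strongest reply is that the subtraction is one generic sentence covering every questionnaire and battery outcome. It already calls post minus baseline an improvement for run times, where lower is better, so direction must be handled outcome by outcome. An analysis plan that is not shown may fold the ratio. Part of this stands: the sentence is not a literal rule that higher is better. But for run times the remedy is a change of sign, and no change of sign repairs a ratio that is worse on both sides of its best value. The article also states both the unfolded definition and the subtraction. A plan that folds would depart from what is published, so the text needs amending either way.

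A second reply is that deficits may share a side. The Praxis group is all right-handed, and a simulated weapon is carried in the POWAR-TOTAL. The article also never says that 1 is the reference; that follows only from calling the measure symmetry. This is fair. It is why the loss is graded and why the directional ratio should still be reported.

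Three stronger readings are tempting and are not supported:
- A reader might infer that the measure cannot detect recovery unless everyone is weak on the same side. Step 3 shows 42% power at 80% left-sided.
- A reader might infer that the minimum important difference is distorted too. It is set at 0.2 times an SD, which has no direction, so nothing cancels; only its scale would change.
- A reader might judge the loss by a paired test within the Praxis group. The article plans paired tests for the questionnaires; the group comparison of battery change uses the general linear model, which is why Steps 3 and 4 compare groups.

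**Conclusion.** The concern holds. As written, the article pairs a ratio that is best near 1 with a change score and a threshold count that both need a single good direction. That follows from the definitions and needs no assumed number.

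The size does rest on assumptions. With an even mix of sides, a 60% reduction, error SD 0.08 and near-symmetric Controls, power is about 5-6% on the raw ratio against 15% to 73% on the folded measure, as the ln-ratio SD goes from 0.10 to 0.25. With an uneven mix the loss is partial, and with deficits all on one side there is none.

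The consequence is moderate. One of five sensor measures is affected, together with the correlations that use its change and its threshold counts. A reader might infer that the study's success criteria are at risk, but those are a mean usability score of 68 or higher and at least 80% of the Praxis group completing all sessions. Neither uses this ratio.

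**What to change.** In the Readiness Assessment Battery section, define the analysed variable as |ln(left velocity / right velocity)|, where 0 is symmetric and lower is better. Use it for change, the group comparison, correlations and the Control reference values, and state that for this outcome meeting the Control reference means a value at or below it. Report the directional left/right ratio descriptively, so that a bias shared towards one side remains visible.

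The cost is one line of text. Both velocities are already recorded, so no new data are needed. There is a small statistical price: the folded measure has a positive noise floor, and it can lose some power if asymmetry is small and mostly on one side. The change should be made before results are seen, because folding afterwards would look data-driven.
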